### Objectives {7}

The primary objective of this study is to comprehensively assess and compare the effectiveness of three distinct BLT approaches for the treatment of depressive symptoms: (1) standard home-based BLT (*Light@Home)*, (2) BLT at the *LightCafé (LightCafé)*, and (3) BLT at the *LightCafé* with personalized timing of light and darkness using BBG (*LightCafé* +).

Secondary objectives are:i.The identification of predictors of treatment response, encompassing baseline clinical characteristics, sleep metrics, circadian parameters, and light-related behaviors.ii.Elucidation of underlying mechanisms of BLT’s efficacy by investigating the contribution of circadian rhythm changes, enhancing our understanding of the complex interactions between mood, energy levels, and sleep within the context of BLT and exploration of the neural effects of BLT by studying both functional and structural brain changes before and after treatment.

Importantly, we are not testing BLT’s efficacy for specific diagnostic categories; rather, we ask whether embedding BLT within a rich psychosocial setting and personalizing its timing can amplify and prolong its antidepressant effect, all while unraveling who benefits most and through which pathways. By moving from “Does BLT work?” to “How can we make it work better, for whom, and why?”, this multicenter RCT will lay the groundwork for personalized and embedded BLT protocols and real-world clinical guidelines.

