## Interventions

### Explanation for the choice of comparators {6b}

This study compares the effectiveness of three distinct BLT administration strategies for treating depression:

I.**Home-Based BLT (*****Light@Home*****)**: Patients receive BLT in their own homes.II.**BLT in LightCafé (*****LightCafé*****)**: Patients undergo BLT in a café-like environment (*LightCafé*), which emphasizes lifestyle improvements alongside the therapy.III.**Personalized BLT in the LightCafé (*****LightCafé +*****)**: Patients receive BLT in the *LightCafé*, with treatment timing tailored to their individual sleep–wake pattern and personalized timing of darkness with the use of BBG.

The *Light@Home* condition serves as an active control condition against which both other conditions will be evaluated. Given that our primary objective is not to measure the effectiveness of BLT in alleviating depressive symptoms per se, but rather to optimize its delivery, the inclusion of a placebo or treatment-as-usual condition in this trial is deemed unwarranted. To assess and possibly control for the difference in expectations of treatments, all participants will complete the Credibility/Expectancy Questionnaire (CEQ; [71]) before treatment onset.

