### Intervention description {11a}

In all study arms, participants are subjected to BLT in adherence to Dutch BLT guidelines [72], utilizing an Innolux LED light Lamp delivering light with an illuminance of 10,000 lx at a distance of 70 cm and a color temperature of 3800 K. BLT sessions, lasting 30 min each, are scheduled from Monday to Friday between 7:30 AM and 10:30 AM.

The number of BLT sessions is contingent upon the individual response of each participant, with a maximum duration of 3 weeks. Initially, participants undergo five consecutive BLT sessions during the workweek. Subsequently, the therapeutic efficacy is evaluated utilizing the QIDS-SR during the Friday session. If the QIDS-SR falls below 6, remission is inferred, leading to the termination of BLT. Alternatively, an additional five sessions are administered. This evaluation and decision process is repeated at the end of the second week. If the QIDS-SR score is still above 6, a third and final week of treatment is provided.

This individualized strategy is intended to reduce the small risk of (hypo)manic switches, which occur in less than 2% of bipolar patients and almost exclusively in those not maintained on mood stabilizers [11, 73]. We will continuously monitor for (hypo)manic symptoms using the Young Mania Rating Scale (YMRS; [74]) and clinical observation: a YMRS score ≥ 13 and clinician‐identified symptoms will lead to immediate treatment cessation, while scores of 10–11 will prompt a joint review with a second clinician to decide on discontinuation [75, 76].

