#### Circadian effects of BLT and their relation to the antidepressant outcomes

To analyze changes in circadian parameters, including DLMO, Phase Angle Difference, inter-daily stability, and intra-daily variability, multilevel mixed-effects models will be employed. The fixed effect’s structure will incorporate time (*Baseline vs. Post-treatment*), and the interaction between time and treatment condition (*Light@Home*,* LightCafé*, and *LightCafé* +). Inclusion of random intercepts for participants and study site and random slopes for time within participants will be evaluated based on model fit criteria, including AIC and BIC. Circadian effects will be compared between timepoints by evaluating the fixed effect of time in the model, while the effect of the treatment condition will be interpreted by assessment of the interaction term between time and treatment condition.

Following the assessment of changes in circadian parameters (e.g., DLMO, Phase Angle Difference, inter-daily stability, and intra-daily variability), multilevel mediation analyses will be conducted to determine whether these changes mediate the relationship between timepoint and depressive symptoms (QIDS-SR). Each mediator will be tested individually using an approach based on Bauer et al. [99] which includes decomposing within- and between-person components to yield valid indirect effect estimates in nested data. We will apply bootstrapping (5000 samples) to estimate the indirect path (ab) and construct 95% confidence intervals for each mediator. In addition, moderation analyses will examine whether baseline depression severity or sleep quality interact with treatment conditions to affect depressive outcomes. Results will report direct effects (c′), indirect effects (ab), and any interaction effects (a × b), along with the corresponding confidence intervals and *p*-values.

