To benchmark the added value the *LightCafé* and the personalized chronotherapeutic interventions, we contrast the two administration strategies against an active home-based control (Light@Home). Opting for Light@Home as our control arm reflects a pragmatic choice: although it precludes attribution of observed effects solely to light exposure, it provides a realistic comparator that mirrors how many patients already receive BLT and is therefore a valuable comparator in our search for optimization of administration. It should however be noted that even though we adhere to Dutch BLT guidelines for depression, the field still lacks consensus on optimal BLT dosing—specifically wavelength, intensity, and overall treatment duration—so true optimized delivery of BLT still warrants further investigation.

Besides these pragmatic, real-life objectives, our study also aims to identify individual characteristics predicting responses to BLT, examining a range of socio-demographic, clinical, sleep-related, circadian, and light-related factors. We will employ advanced statistical techniques to uncover strong predictors of positive outcomes, enhancing clinical decision-making and paving the way for a more personalized approach to BLT. The trial also explores the mechanisms underlying BLT’s efficacy through mediation analysis, assessing whether and how changes in circadian rhythm mediate its antidepressant effects. Using EMA data analyzed via random-intercept cross-lagged panel modelling (RI-CLPM), we will capture real-time fluctuations in mood, sleep, and energy levels, clarifying whether BLT primarily targets mood, sleep, energy, or a combination of these factors. Neurobiological analyses via MRI will further elucidate structural and functional brain changes associated with BLT, including assessments of connectivity and activity patterns.

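### The mediation model takes timepoint as exposure in a trial where every arm receives BLT, so it can show a within-person association but not mediation of BLT's antidepressant effect

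*Protocol article*

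**What the plan says.** The section on circadian effects first models each circadian parameter on time and the time-by-arm interaction, where "the effect of the treatment condition will be interpreted by assessment of the interaction term between time and treatment condition". It then turns to mediation. For DLMO, phase angle difference, inter-daily stability and intra-daily variability, one at a time, it asks whether the changes "mediate the relationship between timepoint and depressive symptoms (QIDS-SR". The estimator is fixed too: "We will apply bootstrapping (5000 samples) to estimate the indirect path (ab", with 95% confidence intervals, a split into within- and between-person components, and separate reporting of the direct effect. Arm is not the exposure in this step. It reappears only in a separate moderation analysis by baseline severity or sleep quality.

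On design, Intervention description {11a} states: "In all study arms, participants are subjected to BLT in adherence to Dutch BLT guidelines". Explanation for the choice of comparators {6b} adds that "the inclusion of a placebo or treatment-as-usual condition in this trial is deemed unwarranted".

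On purpose, Objectives {7} sets out to explain BLT's "efficacy by investigating the contribution of circadian rhythm changes", and the Discussion describes the mediation analysis as "assessing whether and how changes in circadian rhythm mediate its antidepressant effects". The Discussion also says of the Light@Home control that "although it precludes attribution of observed effects solely to light exposure", but does not repeat this limit where it describes the mediation.

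**The concern.** Timepoint is not an intervention. Every participant moves from baseline to post-treatment, and every participant receives BLT in between, so the mean change in mediator and in symptoms contains BLT together with whatever else happens over those weeks. The article itself supplies the alternatives:

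- Entry requires a QIDS-SR score of at least 6 (Eligibility criteria {10}), and QIDS-SR is the mediation outcome, so some regression to the mean is to be expected.
- New treatments and dose changes are discouraged but allowed (Relevant concomitant care {11d}).
- Recruitment runs all year (Recruitment {15}), so season varies between participants.
- Spontaneous recovery from a depressive episode can carry sleep and circadian measures with it.

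At stake is the conclusion on a named secondary objective. The introduction says that earlier attempts to link phase shifts to symptom reduction gave inconsistent results and that this trial aims to clarify the matter. An uncontrolled pre-post indirect effect cannot do so, yet the Discussion would have it read that way.

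**Working it through.** **1. What the model estimates.** With two timepoints, the within-person model reduces to:

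- a = mean change in the mediator;
- b = slope of individual QIDS-SR change on individual mediator change;
- ab = indirect effect; the direct effect c′ takes the rest of the mean QIDS-SR change.

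Hence the expected ab = mean(ΔM) × r × SD(ΔY) / SD(ΔM), where r is the correlation between individual changes. Nothing in this expression distinguishes change due to BLT from change due to anything else.

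**2. The plan's own figure.** No power is stated for the mediation. The nearest figure is for the a path of DLMO (Justification for the saliva sampling sample size): 72 participants, two timepoints, within-person SD 45 min, shift 30 min, alpha 0.05, power 96.40%.

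- SD of the difference = 45 × √2 = 63.6 min.
- Standard error = 63.6 / √72 = 7.5 min; 30 / 7.5 = 4.0.
- Two-sided paired t-test: power 97.6% (normal approximation Φ(4.0 − 1.96) = 97.9%).

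This agrees with 96.40% to within 2 points. The stated power therefore refers to the pre-post shift, not to a contrast between arms.

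**3. Behaviour with no BLT effect.** From the article: n = 72, SD of DLMO change 63.6 min, mean shift 30 min. Assumed, because the article gives no value: mean QIDS-SR change −5 (SD 5), correlation r from 0 to 0.5, and a smaller mean shift of 15 min as an alternative. All change is natural course, and arms do not differ. There were 600 trials per setting with 500 bootstrap samples each (the plan uses 5000) and a percentile interval. The entries are the share of trials in which the 95% interval for ab excludes zero, with timepoint as exposure.

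| r | mean shift 30 min | mean shift 15 min |
|---|---|---|
| 0 | 5% | 3% |
| 0.2 | 43% | 20% |
| 0.3 | 72% | 34% |
| 0.4 | 94% | 45% |
| 0.5 | 98% | 52% |

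Check against the formula, for a 30-min advance and r = 0.3: −30 × 0.3 × 5 / 63.6 = −0.71 QIDS-SR points; the simulated mean was −0.70. That is 0.71 / 5 = 14% of the assumed mean change, and the remainder falls to c′.

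In the same data, with arm as exposure (LightCafé+ against Light@Home), the interval excluded zero in 0.3% to 6% of trials.

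**4. What an arm-based test could detect.** Assuming equal allocation, 72 / 3 = 24 per arm.

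- Standard error of the arm difference in DLMO change = 63.6 × √(2/24) = 18.4 min.
- For 30 min: 30 / 18.4 = 1.63; power = Φ(1.63 − 1.96) = 37%. For 15 min it is 13%, and for 45 min 69%.
- With both LightCafé arms pooled (48 against 24), power for 30 min is 47%.
- For 80% power at 30 min: 2 × (1.96 + 0.84)² × 63.6² / 30² gives 71 per arm; for 90%, 95 per arm.

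**The case against.** Several points on the other side are sound.

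- **Parallel trends alone are harmless here.** A reader might infer that any common drift of DLMO and QIDS-SR yields a significant ab. It does not: b is adjusted for time, and with uncorrelated individual changes the error rate is the nominal 5%. The within-person decomposition also removes stable differences between people. The problem needs correlated individual changes, and the size of that correlation is an assumption.
- **The design limits some rival explanations.** Treatments started within two months are excluded, later changes are to be documented and accounted for, QIDS-SR is repeated at B1 after intake, and the interval is a few weeks under year-round recruitment. This weakens regression to the mean, co-treatment and season, but none of it removes spontaneous recovery.
- **The size cannot be read from the sample-size section.** A reader might divide the assumed effects there (0.25 / 0.33 = 76%, 0.25 / 0.40 = 63%) and say that the timepoint model credits all this shared change to the pathway. The documents do not support that. Those inputs belong to the MADRS power simulation and not to QIDS-SR, the Light@Home change occurs under active BLT and so is not a measure of natural recovery, and c′ is reported separately from ab.
- **Using arm as exposure does not answer the mechanism question.** A reader might infer that it would. It tests only whether circadian change explains differences between delivery models; BLT against no BLT is not identified by any analysis in this design. Its b path also stays observational, and the LightCafé arms add coaching and social contact.
- **The limit is partly conceded.** The Discussion admits it for the choice of comparator and time-by-arm effects are tested for each circadian parameter, but neither is carried into the mediation claim.

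These points narrow the concern and change the remedy. They do not rescue the inference that the Discussion draws.

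**Conclusion.** The point holds as a limit on inference. With timepoint as exposure, BLT in every arm and no untreated arm, a non-zero ab cannot show that circadian change mediates BLT's antidepressant effect. It shows that people whose circadian measures changed more also improved more or less, in a sample whose mean moved. With 72 participants and a 30-minute mean DLMO change, a correlation of 0.2 to 0.4 unrelated to BLT makes the interval exclude zero in about 43% to 94% of trials; with a 15-minute change the range is 20% to 45%. These figures rest on the assumed correlation and on an assumed QIDS-SR change of −5 (SD 5). They illustrate how readily the test can mislead and are not a forecast for this trial. The primary comparison is unaffected; the conclusion on a secondary, mechanistic objective is not supported as worded.

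**What to change.** 1. In the section on circadian effects, describe the timepoint model as a within-person association between circadian change and symptom change. Remove from that section, from Objectives {7} and from the Discussion the inference that it shows mediation of BLT's effect. Carry over the limit already conceded for the comparator.
2. Add a supplementary mediation analysis with randomised arm as exposure: arm to change in mediator to change in QIDS-SR, adjusted for baseline mediator and baseline QIDS-SR. State that it addresses only differences between delivery models.

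No new data are needed; the cost is wording and one more analysis. The supplementary test has real weaknesses that should be stated with it. Its b path remains observational. DLMO and phase angle difference are available in only 72 participants, with about 37% power for a 30-minute arm difference in DLMO shift, whereas the actigraphy-based mediators are planned for all participants. LightCafé+ also aims at advance, delay or no shift according to the individual, so its mean effect on DLMO may be small even if personalisation works. A null result there should not be read as evidence against a circadian pathway.

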#### Dynamics of sleep, affect, and energy levels throughout therapy

The primary objective of the EMA is to investigate the dynamic interplay between sleep, affect, and energy levels during BLT. We aim to uncover whether the antidepressant effects of BLT primarily result from improvements in mood, sleep, daytime energy levels, or a combination of these factors. For statistical analysis, we will first calculate daily averages for all momentary measures. If fewer than three measures are available for a given day, the daily average will be set to not applicable (*NA)*. To isolate within-person variability, all measures will subsequently be person-mean-centered. Additionally, baseline measures—such as depressive symptoms and sleep quality—will be grand-mean centered.

To analyze the data, we will specify a Random Intercept Crossed-Lagged Panel Model (RI-CLPM) that focuses on the relationships between sleep parameters, affect, and energy levels over time. This model will incorporate dynamic variables, specifically the person-mean centered scores for sleep parameters, affect, and energy levels measured at the day level, alongside trait variables represented by grand-mean centered scores from baseline assessments, including severity of depressive symptoms and sleep quality. The model structure will include random intercepts for each participant, autoregressive paths to assess the stability of each variable, and cross-lagged paths to evaluate how one variable at a previous time point influences another variable at a subsequent time point. To estimate the RI-CLPM, we will utilize the *lavaan* package in R, employing maximum likelihood estimation for model fitting.

Prior to model construction, we will conduct an exploratory analysis to identify the most relevant parameters related to sleep, affect, and energy levels for inclusion in the model. This step is crucial to ensure that we accurately measure the constructs involved and capture the dynamics effectively. The exploratory analysis will involve visualizations, such as time series plots, lag plots, and scatter plots, to assess relationships and patterns in the data. Additionally, we will investigate how the variables change over time, seeking patterns in daily fluctuations and overall trends throughout the therapy period. Correlations between different variables at various time scales will also be examined to identify initial relationships that could inform model selection.

Based on the findings from the exploratory analysis, we will construct a model that best represents the dynamics of sleep, affect, and energy levels. We may incorporate covariates and trait-level variables, such as demographic factors, baseline depressive symptoms, and sleep quality, which could influence the relationships being studied. In our reporting, we will present the overall model fit indices (e.g., comparative fit index, Tucker–Lewis index, root mean square error of approximation) to assess the adequacy of the RI-CLPM. We will detail the autoregressive paths indicating the stability of each variable over time, as well as the cross-lagged paths, which reveal how changes in one variable at a previous time point influence changes in another variable at a subsequent time point. This systematic examination aims to enhance our understanding of the therapeutic mechanisms underlying BLT and how improvements in sleep, affect, and energy levels interact throughout the treatment process.

Following the data analysis, we will conduct a post hoc power analysis to evaluate the power of the RI-CLPM. If this analysis reveals insufficient power, we have the option to revert to a mixed model approach, which necessitates fewer participants to achieve similar power levels.

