### The chronobiological and neurobiological mechanisms underlying BLT

Next, this study aims to examine the mechanisms by which BLT alleviates depressive symptoms, as currently no theory has conclusively explained its effects. The most widely accepted framework—the chronobiological phase-shift hypothesis—proposes that BLT realigns the circadian system with the natural 24-h light–dark cycle [29], correcting rhythm disturbances common in major depressive and bipolar disorders [30–33], and thereby alleviating depressive symptoms. Although robust phase advances following morning BLT have been reliably documented [34], attempts to link these shifts directly to reductions in depressive symptoms have yielded inconsistent results [35–40]. Several other studies further challenge a circadian explanation, suggesting that light exerts its mood-enhancing effects through neural pathways independent of the central clock [17, 41–43], or via directly altering the serotonin release [44, 45]. Consequently, while BLT is often framed as a chronotherapeutic intervention, key questions persist about the true role—and relative importance—of underlying chronobiological mechanisms which we aim to clarify in the current trial.

Light’s impact on sleep quality and energy levels may provide an additional—and potentially contrasting—route by which BLT exerts its antidepressant effects. Up to 90% of depressed patients report insomnia, delayed sleep onset, and fragmented rest at night [46, 47], while many also suffer daytime sleepiness [48]. Controlled trials show that daily morning BLT consolidates sleep, shortens sleep-onset latency, and improves alertness during the day [49, 50], but complicated by the multidirectional associations between mood, sleep, and energy levels [51–53], it remains unclear whether these changes stem from circadian stabilization, light’s direct alerting effects [54, 55], a synergistic interplay of both, or an unknown mechanism. By tracking light exposure, sleep, energy, and mood on a day-to-day level in the current trial, we aim to map how these factors interact with each other over time and gain insight into each one’s role in BLT’s antidepressant mechanism.

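### The RI-CLPM that is to show whether BLT works through mood, sleep or energy lists no term for light, session or treatment phase, so its paths cannot support that conclusion

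*Protocol article*

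**What the plan says.** The aim, in *Dynamics of sleep, affect, and energy levels throughout therapy*, is: "We aim to uncover whether the antidepressant effects of BLT primarily result from improvements in mood, sleep, daytime energy levels, or a combination". The Discussion repeats it as the expected product of the RI-CLPM: "clarifying whether BLT primarily targets mood, sleep, energy, or a combination of these factors".

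The same methods section lists the model:
- The dynamic variables are "the person-mean centered scores for sleep parameters, affect, and energy levels measured at the day level", and beforehand "all measures will subsequently be person-mean-centered".
- On structure: "The model structure will include random intercepts for each participant, autoregressive paths to assess the stability of each variable, and cross-lagged paths".
- Baseline severity and sleep quality enter as trait variables.
- Further terms are optional: "We may incorporate covariates and trait-level variables, such as demographic factors, baseline depressive symptoms, and sleep quality".

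The background section on mechanisms names light as part of the day-level picture: "By tracking light exposure, sleep, energy, and mood on a day-to-day level in the current trial". *Light-related parameters* defines daily light summaries, among them light in the 3 h after waking. EMA and the light sensor both run through the baseline, treatment and post-treatment weeks.

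**The concern.** The question is which of three variables carries the effect of a treatment, but the model has no variable for that treatment: no light, session, treatment day, phase or arm. Its cross-lagged paths describe how sleep, affect and energy follow one another from day to day in depressed people. Such paths could look the same with or without light.

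Two consequences need checking: what a BLT effect shared by everyone does to the paths, and what improvement that differs between people does to them. At stake is a secondary mechanistic claim, in which ordinary sleep-mood dynamics could be reported as the way BLT works.

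**Working it through.** **Inputs from the document** (*Justification for the EMA sample size*): 14 time points, ICC 0.3, random-intercept correlation 0.3, within-person correlation 0.5, autoregression 0.4, cross-lag 0.3, N = 120. Alpha is 0.05, taken as two-sided.

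**Assumed, because the document gives no figure:** 7 untreated then 7 treated days; size, correlation and timing of person-specific improvement.

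**Model.** For person i on day t, y_it = μ_t + b_i + w_it and w_it = Φ w_i,t−1 + u_it, with y = (sleep, affect). Within-person variance is 1, so the random-intercept variance is ICC/(1 − ICC) = 0.3/0.7 = 0.429. The random intercepts remove the person means here. Centring each person first as well makes the 28-column covariance matrix singular (rank 26 with complete data).

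**The plan's own figure.** With lags free per day, Wald power for a cross-lag of 0.3 on the weakest path is 0.851, 0.882 and 0.907 at N = 100, 110 and 120. The stated power of over 90% at 120 is reproduced. It does not bear on the present point.

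**1. Effect common to all participants.** It replaces μ_t by μ_t + δ on treated days. Adding a constant leaves Cov(y) unchanged, and with free means Φ is estimated from Cov(y) alone. One simulated dataset (N = 120, true lags 0.4/0.3) with a 1-SD shift from day 8 gives:

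| Shift placed on | Means | sleep→sleep | affect→sleep | sleep→affect | affect→affect |
|---|---|---|---|---|---|
| none, sleep, affect or both | free | 0.451 | 0.278 | 0.379 | 0.369 |
| none | equal | 0.454 | 0.277 | 0.377 | 0.368 |
| sleep only | equal | 0.632 | 0.196 | 0.272 | 0.409 |
| affect only | equal | 0.482 | 0.209 | 0.289 | 0.575 |
| both | equal | 0.511 | 0.324 | 0.437 | 0.418 |

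Free means: the four scenarios cannot be told apart. Equal means: the shift contaminates the paths.

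**2. Improvement that differs between people.** Cov(y) becomes Σ + L G L′, where L switches on from day 8 and G holds the variances and covariance of the improvements. The standard model was refitted to this matrix with true cross-lags 0, autoregression 0.4, within-person correlation 0.5 and lags held equal over time. Two fits differ only in whether the daily residual variances and covariances are free or held equal. The percentage is the chance of a significant false path at N = 120.

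| SD of improvement (both series) | Correlation | Cross-lag, residuals free | Cross-lag, residuals equal |
|---|---|---|---|
| 1 | 0 | −0.089 (94%) | −0.077 (79%) |
| 1 | 0.5 | +0.001 (5%) | +0.001 (5%) |
| 1 | 0.8 | +0.065 (60%) | +0.055 (43%) |
| 0.5 | 0 | −0.029 (18%) | at most about 0.03 in size |
| 0.5 | 0.5 | 0.000 (5%) | as above |
| 0.5 | 0.8 | +0.019 (10%) | as above |

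Checks with 200 simulated datasets gave 88% and 54% for SD 1 at correlations 0 and 0.8, 6.5% for SD 0.5 at correlation 0.8, and 7.5% with no improvement at all.

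Unequal or staggered improvement, SD 1, residuals free:
- Only sleep improvement varies: affect→sleep −0.110 (95%).
- Sleep early, affect late, correlation 0.8: sleep→affect +0.065 (65%).
- True lags 0.4/0.3, uncorrelated improvements: the cross-lags of 0.3 shrink to 0.161.

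Autoregression is inflated for every series whose improvement varies (0.42 to 0.62 against a true 0.4).

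**3. With the missing term.** Adding a person-specific phase component per series returns the true values in the population fit (cross-lags 0.000, autoregression 0.400). Power for a cross-lag of 0.3 at N = 120 is then 0.71-0.90 per path with lags free per day, and about 1.00 with lags held equal.

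**The case against.** **The specification is open.** An exploratory step precedes model building and includes looking at trends over therapy. The covariate list is illustrative, and the statistical section calls itself an initial framework. A phase or trend term could still be added. That is fair, and details of detrending may be left to an analysis plan. But every named example is a baseline or trait variable, while the mechanism conclusion is stated firmly in both places.

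**Light is not absent from the whole plan.** A reader might infer that it is. The document does not support this: one light window is tied to EMA prompts, and *Methods for additional analyses* uses sensor-based adherence as a covariate for change in symptoms, sleep and circadian phase. Other sections model sleep and QIDS-SR by time and arm, and mediation by circadian parameters. None of these links daily light to affect or energy, and none is connected to the RI-CLPM paths.

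**The paths are not worthless for mechanism.** If BLT acted wholly through sleep, a sleep-to-affect path would have to exist, so its absence would count against that route. This stands. Its presence, however, would not show that BLT uses the route.

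**False cross-lags are not inevitable.** It is tempting to say that unmodelled improvement must create them, especially where sleep and mood improve together. The figures do not support that: the bias can be positive, negative or nil, and at SD 0.5 it is small beside the planned cross-lag of 0.3.

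**Conclusion.** The point holds for the mismatch between aim and model. With free occasion means, the lag paths carry no trace of a common BLT effect; this is algebra and needs no assumed figure beyond the effect being the same for everyone on each day. With equal means, they are distorted instead. Neither version identifies which variable BLT moves.

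The bias from person-specific improvement is conditional. For equally variable, simultaneous improvements it runs from about zero to roughly 0.05-0.09 in size at SD 1 and is at most about 0.03 at SD 0.5, with either sign. It vanishes when improvements correlate as the daily fluctuations do (0.5). Those SDs, correlations and the 7/7 split are assumptions. Only the inflation of autoregression is general to series whose improvement varies.

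This concerns a secondary analysis in 120 participants. Nothing here touches the primary MADRS comparison or the stated EMA power for the model as listed.

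**What to change.** 1. Enter measured daily light (for example the light in the 3 h after waking that the protocol already defines) and a treatment-phase indicator as time-varying predictors of affect, energy and the following night's sleep. Include the weekend/weekday factor already planned for the sleep models. Session yes/no alone will not do: sessions run Monday to Friday, so within treatment weeks it nearly coincides with weekday.
2. Model person-specific change with a phase or trend component per series, and hold the lags equal over time.
3. If paths are compared between the baseline and treatment weeks, describe the comparison as uncontrolled, since no arm goes without BLT.
4. Limit the mechanism statements in the methods section and the Discussion to what these terms show. Otherwise describe the RI-CLPM as day-to-day dynamics during BLT.

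**Cost.** Plan wording and extra modelling before the EMA data are analysed; no new data. The price is in power: with lags free per day, the person-specific component takes N = 120 below the planned 90% per path (0.71-0.90). Equal lags avoid this (about 1.00) but assume that the dynamics do not change over the window. If none of this is wanted, item 4 alone removes the contradiction.
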